Possible risk factors for a prolonged total interval could be patient, tumour or healthcare system characteristics. In order to study the latter, it is informative to compare patients from different countries. In both the Netherlands and UK, general practitioners (GPs) have an important role as healthcare gatekeepers. In general, people consult their GP who then decides whether referral is warranted and determines the acuteness and location of the referral. In the UK, privately insured patients can also self-refer to a hospital without seeing a GP. Furthermore, within the UK, a considerable amount of patients with cancer is diagnosed at an emergency department, associated with worse outcomes.^11^ Sarcoma care is formally centralised within the UK, whereas the Netherlands has bone sarcoma centres, and referral to dedicated STS centres is encouraged, but not commissioned. Furthermore, cultural differences may play a role in patient behaviour. Also, longer travel time to a sarcoma centre in the UK compared with the Netherlands may also affect total interval length.

Up to now, only few studies regarding total interval length and clinical outcomes in sarcoma have been published, most were retrospective and included mainly children. Some studies found that a longer total interval worsened OS, while others did not find inferior clinical outcomes.^10^ Researchers have argued that this lack of an association, often referred to as the ‘waiting-time paradox’, may be because the studies have not been able to adequately adjust for the aggressiveness of the cancer tumours. The most significant effect of a long interval for sarcomas seems to be the increasing size of the lesion,^12^ with consequent decreased chance of uncomplicated resection with clear surgical margins, a greater risk of amputation and increased risk of developing metastases.^13^ This may also affect patient-reported outcomes such as HRQoL of patients with sarcoma.

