### Case report forms

CRFs will be completed at five time points during the study. The first will be completed on inclusion, the following time points coincide with the completion of follow-up questionnaires. The last CRF is also the end-of-study CRF, which can be completed before 24 months if a patient withdraws or deceases. The information collected on the CRF will be stored on a secure CRF database using anonymous study numbers. Data collected includes documentation of eligibility criteria, date of diagnosis, tumour characteristics such as histology, tumour, node and metastasis (TNM) stage, tumour size, treatment regiment, re-occurrence of disease or metastases, reason for withdrawal of the study and time of death, if applicable.

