### Endpoints

The primary endpoint is HRQoL of patients with sarcoma at diagnosis (baseline) as measured with the EORTC QLQ-C30 (global health status). Secondary endpoints are: QALY, psychological distress, stage and tumour size at diagnosis, PFS and OS.

If subgroups are large enough, we will conduct these analyses for different clinically relevant subgroups, such as different histological subtypes, geographical areas, and so on.

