### Statistical analysis

Descriptive statistics (means, SD, median, range, frequencies) will be used to quantify diagnostic intervals and describe the study population.

HRQoL at baseline will be calculated according to the EORTC scoring manual.^43^ Missing items will be imputed according to these guidelines, after which an available case analysis will be performed.

The relationship between total interval length and HRQoL at baseline will be investigated by plotting HRQoL against total interval length as a continuous variable. Linear regression will be used to assess their association. The time point providing a significant difference in HRQoL will be used as a cut-off point for further analysis. If this does not provide a clear cut-off point, logistic regression will be used to assess an association between baseline HRQoL and total interval grouped into suitable categories, such as quartiles. The last quartile will then be used to define the population with a long interval.

Apart from statistical significance, we will look at clinically relevant differences in HRQoL scores as determined by Cocks *et al.*^42^ A small effect size will then be considered as an appropriate value for a cut-off point.

A series of univariate logistic regression analyses will be conducted to assess the relationship between total interval length (grouped by the cut-off point as defined by the previous analysis) and independent variables, such as patient, tumour and healthcare system risk factors. All factors with p<0.1 will then be used in multiple logistic regression analysis (forced entry method) to investigate whether these factors are independently associated with total interval length.

Apart from total interval length, the association of other patient and tumour characteristics (such as self-efficacy, social support, financial difficulties, histology), and HRQoL at baseline will be investigated using univariate logistic regression analysis. Using the forced entry method, multiple logistic regression analysis will then be performed with all factors with p<0.1 to assess what factors are independently associated with baseline HRQoL.

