Change in HRQoL during the follow-up period of 2 years and factors associated with changes in HRQoL will be analysed using repeated measures mixed models. This will be compared between patients with a short and long total interval, using repeated measures analysis of variance, controlling for relevant patient and tumour characteristics, and the patient’s baseline score. Clinically relevant differences will be assessed using Cocks’ method.^41 42^

Other patient-reported outcomes such as QALYs and psychological distress will be analysed in the same way.

Multivariate analyses will be performed to examine associations between total interval length and (1) QALYs, (2) psychological distress, (3) stage at diagnosis and (4) tumour size. These analyses will be corrected for potential confounders including patient and tumour characteristics and healthcare system.

Both unadjusted and adjusted multivariate Cox proportional hazard regression analyses will be used to examine whether a long total interval is associated with PFS or OS.

PFS is defined as the time interval between diagnosis until clinical or radiological progression, as assessed by the treating consultant. OS is defined as the time from diagnosis until death.

Statistical analyses will be performed using IBM SPSS V.25.0; two-sided p values <0.05 will be considered statistically significant.

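### The primary analysis of total interval and baseline HRQoL names no covariates, and no other model guarantees an adjusted interval estimate

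*Protocol article*

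**What the plan says.** All references are to the Protocol article.

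- **Endpoints:** the primary endpoint is baseline QLQ-C30 global health status. Stage and tumour size at diagnosis are secondary endpoints.
- **Statistical analysis, primary association:** HRQoL is plotted against total interval as a continuous variable, and "Linear regression will be used to assess their association". The time point that gives a significant HRQoL difference becomes the cut-off for further analysis. If none is clear, "logistic regression will be used to assess an association between baseline HRQoL and total interval grouped into suitable categories, such as quartiles". Neither model names a covariate.
- **Statistical analysis, multivariable baseline HRQoL model:** the paragraph is introduced as dealing with characteristics other than total interval. After univariate screening, "multiple logistic regression analysis will then be performed with all factors with p<0.1 to assess what factors are independently associated with baseline HRQoL". The model that identifies risk factors for a long interval uses the same p<0.1 screen.
- **Statistical analysis, other outcomes:** for QALYs, distress, stage and tumour size, "These analyses will be corrected for potential confounders including patient and tumour characteristics and healthcare system". PFS and OS get unadjusted and adjusted Cox models. The comparison of HRQoL change between short and long interval controls for patient and tumour characteristics and the baseline score. No p-value screen is stated for any of these.
- **Introduction:** the absence of an association in earlier studies "may be because the studies have not been able to adequately adjust for the aggressiveness of the cancer tumours".
- **Case report forms:** the data collected include "tumour characteristics such as histology, tumour, node and metastasis (TNM) stage, tumour size".

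**The concern.** The protocol identifies one source of bias that could make an observational comparison of interval and outcome uninterpretable: fast-growing tumours are diagnosed sooner and do worse. It plans adjustment for the secondary outcomes and for HRQoL change, but as written leaves the primary association crude.

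The multivariable baseline HRQoL model does not close the gap. If total interval is not in it, there is no adjusted interval estimate for the primary endpoint. If it is in it but must pass the screen, a crude association masked by confounding decides whether it enters. The text does not say which applies. The model is also logistic for a 0-100 score with no stated dichotomy, so it would not return an effect in points in either case.

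The consequences go beyond one estimate. The crude HRQoL analysis sets the long-interval cut-off, which then defines the groups in the risk-factor model and the short-versus-long comparisons.

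**Working it through.** **1. The plan's own figure.** Sample size calculation gives a 10-point difference, SD 20, two-sided alpha 0.05, power 0.90 and 25% with a long interval. Long group: (1.960+1.282)² × 20²/10² × (1+1/3) = 10.507 × 4 × 1.333 = 56.0. Total: 4 × 56.0 = 224.2 analysable. The stated 265 follows approximately from 224.2/0.85 = 264 (15% loss, not stated) or 224.2 × 1.20 = 269. The stated 80% response gives 224.2/0.80 = 280. Whichever was used, this is a comparison of two means without covariates. The target is 265 per country, 530 in all.

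**2. Bias of the crude slope.** These inputs are assumptions; none is in the documents:
- L: log interval, in SD units. A: aggressiveness, in SD units, with correlation -r with L.
- Global health = constant - 4L - cA + error, error SD 19.
- r = 0.2 or 0.4; c = 4 to 8 points per SD.

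Expected crude slope = -4 + r × c. Crude residual SD = √(19² + c²(1-r²)), and SE = SD/√N. Adjusted SE = 19/√(N(1-r²)), with A measured without error. Power is for a significant result in the correct direction.

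| r, c | Crude slope | Crude SE, N=265 | Crude power, N=265 | Crude power, N=530 | Adjusted power, N=265 |
|---|---|---|---|---|---|
| 0.2, 4 | -4+0.8 = -3.2 | 19.40/16.28 = 1.19 | 77% | 97% | 92% |
| 0.4, 6 | -4+2.4 = -1.6 | 19.78/16.28 = 1.22 | 26% | 46% | 88% |
| 0.4, 8 | -4+3.2 = -0.8 | 20.37/16.28 = 1.25 | 9% | 15% | 88% |

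Simulation of the same model at N=265 gave 78%, 26% and 8% crude, and 91%, 87% and 87% adjusted.

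**3. No true effect.** The crude slope is then r × c = +0.8, +2.4 or +3.2. At N=265 the chance of a significant apparent benefit of a long interval is about 10%, 51% and 72%, against 2.5% in that direction if the test were valid.

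**4. A second model, on the plan's 25/75 split.** Also assumed: 40% aggressive tumours; long interval in 10% of aggressive versus 35% of other tumours (strong) or 17.5% versus 30% (weak), both giving 25% long overall; aggressiveness lowers HRQoL by 5, 10 or 15 points; residual SD 20; N=225. In the strong case the aggressive share is 0.4×0.10/0.25 = 16% of the long group and 0.4×0.90/0.75 = 48% of the short group, so the bias is 0.32 × 5 to 15 = 1.6 to 4.8 points. In the weak case (28% versus 44%) it is 0.16 × 5 to 15 = 0.8 to 2.4 points.
- True difference -10: the crude estimate is -9.2 to -5.2, with simulated power 84% down to 37%. Pre-specified adjustment gives about -10 and 86-90%.
- True difference 0: crude false-positive rate 6% to 32%.
- Screening the confounder at p<0.1, with interval kept in the model and true difference -10: estimate -9.0 to -10.1, power 81-89%. The screen drops mainly the 5-point confounder, which passes in 22-37% of samples, and leaves at most about 1 point of bias.

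The main loss comes from having no adjustment. Screening the confounders is a smaller matter.

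**The case against.** **The article never says the regression is unadjusted.** This is inferred from silence, and the full plan might add covariates. That caution stands. However, the same section states adjustment for each other outcome analysed against the interval and omits it only here.

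**The size rests on inputs that the documents do not give.** This stands. The Introduction offers aggressiveness as a possible explanation that researchers have argued, in a discussion of survival and clinical outcomes rather than HRQoL. With weak confounding and both countries pooled, crude power is 97%; the slope is still biased (-3.2 against -4).

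**Stronger readings that the documents do not support:**
- *That total interval will be dropped by the p<0.1 screen.* The screen is described for the other factors. What is established is that the interval's place in that model is undefined.
- *That no adjusted HRQoL model exists without a screen.* The model for HRQoL change is adjusted with no screen stated. The gap concerns baseline HRQoL.
- *That stage and tumour size will be adjusted for, removing the effect.* No passage says so. The Introduction and Endpoints treat them as outcomes, and the Case report forms section is a list of data collected. The wording on correction for tumour characteristics simply does not exclude them.
- *That the crude result will be reversed.* With the assumed true slope of -4, every expected crude slope stays negative. An apparent benefit is expected only if the true effect is small or absent.

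**Conclusion.** The concern holds for the primary baseline analysis. As written, the association of total interval with baseline global health is estimated without covariates, that estimate sets the long-interval cut-off, and no other model guarantees an adjusted interval effect on this endpoint. This leaves the primary result open to the explanation that the Introduction reports for earlier null studies.

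The direction of bias, toward zero or toward an apparent benefit of a long interval, depends on aggressive tumours both shortening the interval and lowering HRQoL. The size depends on assumed strengths: it ranges from modest (slope -3.2 for a true -4) to severe (-0.8). The adjusted power figures are an upper bound, because they assume that aggressiveness is measured perfectly. The p<0.1 selection of confounders is a secondary weakness.

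**What to change.** 1. Make the primary model a linear regression of global health on total interval, adjusted for a pre-specified set: age, sex, comorbidity (SCQ), education, bone versus soft tissue, grouped histology and country, with grade if it is recorded. Show the crude estimate beside it, and base any cut-off on the adjusted model.
2. In the multivariable baseline HRQoL model, always include total interval and replace the p<0.1 screen with the fixed set.
3. In the risk-factor model for a long interval, always keep country, since the Sample size calculation sets the per-country targets so that countries can be compared.
4. State that the tumour characteristics adjusted for in total-effect models exclude TNM stage and tumour size. Any analysis that includes them should be labelled as mediation.

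**Cost.** This is a change of wording and uses a few degrees of freedom. Comorbidity, education and histology are listed as collected, and country follows from the centre. The article does not list age and sex by name among the items collected, nor grade, so their recording should be confirmed. Under the assumptions of the second model, keeping 90% power needs about 229-244 analysable patients instead of 224, below 265 if that figure counts baseline completers. Residual confounding will remain, because histology and grade are only proxies for aggressiveness, and the report should say so.

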### Sample size calculation

We expect a minimum response rate at baseline of 65%, based on rates in other PROFILES studies.^40^ During follow-up, after completion of the first questionnaire, we expect a response rate of 80%. The definition of a long total interval will follow from our statistical analysis (see below), however, if the analysis does not provide a clear cut-off point, we will use the last quartile to define the population with a long total interval.

Using the EORTC QLQ-C30, differences of at least 10 points have been considered as clinically meaningful.^41^ Based on results from our ongoing PROFILES studies, an SD of about 20 points for each scale can be expected. Using an alpha of 0.05, a power of 0.90 and a long diagnostic interval of 25% in the total group of patients with sarcoma, with the expected drop-out, would require 265 patients.^42^ In order to make country-to-country comparisons, we aim to include 265 Dutch and 265 English patients in a time frame of 18 months with a total follow-up of 24 months.

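### The long-interval cut-off is chosen by significance on baseline HRQoL, the primary endpoint, so the baseline long-versus-short contrast is circular and the assumed 25% group is not assured

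*Protocol article*

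**What the plan says.** All references are to the protocol article.

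- **Endpoints:** the primary endpoint is baseline HRQoL, measured as QLQ-C30 global health status.
- **Statistical analysis, first step:** baseline HRQoL is plotted against total interval as a continuous variable and a linear regression is fitted.
- **Statistical analysis, cut-off:** "The time point providing a significant difference in HRQoL will be used as a cut-off point for further analysis". If no clear cut-off emerges, interval is grouped into categories such as quartiles and the last quartile counts as long. Published thresholds for clinically relevant differences are then brought in: "A small effect size will then be considered as an appropriate value for a cut-off point".
- **Sample size calculation:** repeats the fallback ("we will use the last quartile to define the population with a long total interval") and plans on a 25% long group, with "differences of at least 10 points have been considered as clinically meaningful".
- **Reuse of the grouping:** it is the outcome in the risk-factor logistic models and defines the short-versus-long comparison over two years, which controls for the patient's baseline score. It also enters the survival models: "Both unadjusted and adjusted multivariate Cox proportional hazard regression analyses will be used to examine whether a long total interval is associated with PFS or" (the sentence ends by naming overall survival).
- **Error rate:** "two-sided p values <0.05 will be considered statistically significant". No adjustment for choosing the cut-off is described.

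**The concern.** The exposure groups are formed by looking for a split of total interval that separates the primary outcome. Comparing baseline HRQoL between those groups then tests a difference that was the condition for forming them. The p value and the size of the difference are both biased towards an effect.

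The rule also cannot be carried out as written. A fitted straight line has one slope and no time point at which a difference becomes significant, so splits have to be tried one after another. The plan does not say how many, over what range, in which direction, what makes a cut-off clear, or how the significance criterion and the small-effect criterion combine. Two analysts could form different groups from the same data.

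What is at stake is the definition of a long interval, which the study carries into its other aims, and the power statement, which presumes a group size and a difference that a searched cut does not guarantee.

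**Working it through.** **1. Inputs.** From Sample size calculation: "Using an alpha of 0.05, a power of 0.90 and a long diagnostic interval of 25" per cent; "an SD of about 20 points for each scale can be expected"; a 10-point difference; 80% follow-up response; 265 patients per country (530 in all). From Statistical analysis: two-sided 0.05. Not in the document, and therefore assumed: the number of candidate cuts, the correlation of later outcomes with baseline HRQoL, and a numerical value for a small effect.

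**2. The plan's own figure.** With long:short = 1:3,

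n(short) = (1 + 3) × 20² × (1.960 + 1.282)² / 10² = 168.1, rounded up to 169; n(long) = 57; total 226.

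Allowing 20% drop-out, 226/0.80 = 282.5, so 283, not 265. A 15% loss would give 226/0.85 = 265.9, so 266, but 15% is not stated. The stated 265 is thus not reproduced exactly. The present point does not depend on it.

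**3. Chance of a false cut-off.** HRQoL was simulated as normal with SD 20 and independent of interval (10,000 data sets per row). The split with the largest |t| was tested at two-sided 0.05.

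| Cuts searched (assumed) | False significant cut, N=265 | N=530 | Mean spurious difference when significant, N=265 |
|---|---|---|---|
| 3 (quartile limits) | 12.5% | 12.6% | 6.4 points |
| 9 (deciles) | 24.7% | 25.5% | 7.5 points |
| all in the inner 80% | 43.7% | 44.9% | 7.5 points |

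Repeat runs agreed within about one percentage point. A hand check supports the last column. A cut is significant only if the difference exceeds 1.97 × SE. At N=265 an even split has SE = 20 × √(4/265) = 2.46, so the difference must exceed 4.8 points. With 10% long, SE = 4.10 and it must exceed 8.1 points. Any selected cut therefore shows at least about 5 points, even when the truth is zero.

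**4. What is carried forward (N=265, no association).** The best cut was applied to other outcomes.

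| Test using the searched grouping | 9 cuts | inner 80% |
|---|---|---|
| follow-up HRQoL, unadjusted (assumed r = 0.5) | 10.2% | 13.8% |
| change from baseline (assumed r = 0.5) | 9.8% | 13.2% |
| follow-up HRQoL, adjusted for baseline score | 5.1% | 4.7% |
| other outcome, r = 0.6 with baseline HRQoL | 12.1% | 18.2% |
| other outcome, r = 0.3 | 7.0% | 8.5% |
| other outcome, r = 0 | 4.9% | 5.4% |

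This table always carries the best cut. In a rerun that switched to the last quartile whenever no cut was significant, the first row became 8.1% and 11.2%, and the adjusted row stayed at about 5%. With only three cuts the first row is about 7% without the fallback and 5.5% with it.

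**5. Power when the cut is not the planned one.** With 265 analysed, SE = 20 × √(1/n(long) + 1/n(short)) and power = Φ(difference/SE − 1.96).

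- 25% long, 10 points: SE = 20 × √(1/66.25 + 1/198.75) = 2.84; Φ(3.52 − 1.96) = 94%.
- 10% long, 10 points: SE = 20 × √(1/26.5 + 1/238.5) = 4.10; Φ(2.44 − 1.96) = 69%.
- 25% long, 5 points (assumed meaning of small): Φ(1.76 − 1.96) = 42%.

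**The case against.** The strongest reply is that the main question is already answered properly. The association between interval and baseline HRQoL is to be assessed by linear regression on the continuous interval, before any cut-off is chosen, and that test keeps its 5% error rate. This stands.

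Two stronger readings are tempting, and the document does not support them.

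- A reader might infer that false positives are inflated in every grouped analysis. Inflation passes only to outcomes correlated with baseline HRQoL, and the article gives no such correlation for PFS, OS or the risk factors. For stage and tumour size it speaks only of total interval length, so use of the cut-off there is not explicit.
- A reader might infer that all later HRQoL comparisons are circular. The two-year comparison controls for the patient's baseline score, and with that adjustment the error rate stayed near 5%.

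It is also fair to say that the last quartile is an ordered fallback rather than a rival rule, and that 44% belongs to the densest search of the three. The mildest assumption gives about 13%.

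The fallback does not rescue the rule, however. It applies only when the search has failed, so it leaves the chance of a false cut-off unchanged, although it softens what is carried forward. Nor is this detail left to a fuller plan: the article states the rule, and a fuller plan could not keep it validly without a correction or a validation step.

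**Conclusion.** Wrong as written, for the cut-off rule and the baseline contrast that follows from it. With no true association, the rule yields a significant cut-off in about 13% of studies if three splits are tried, 24 to 25% for nine and 44% for a dense search, against 5%. The accompanying spurious difference averages about 6 to 7.5 points at N=265, not far below the 10 points that the plan treats as meaningful. Unadjusted or change-score follow-up HRQoL is inflated to roughly 8 to 14% with nine or more splits and an assumed correlation of 0.5. The group size and difference behind the power statement are no longer assured: 94% power can fall to about 69% or 42% in the two cases shown.

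These sizes rest on assumed search grids, normal scores, assumed correlations and an assumed 5 points for a small effect. The direction of the fault does not: trying more than one split at an uncorrected 0.05 exceeds 5%. The continuous regression, the baseline-adjusted longitudinal comparison and analyses of outcomes unrelated to HRQoL are not impugned.

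**What to change.** 1. Delete the significance-based rule and the small-effect rule for choosing the cut-off.
2. Take inference on interval and baseline HRQoL from the continuous regression already planned, with a check for non-linearity.
3. Wherever a long-interval group is used, fix it in advance as the plan's own last quartile, without reference to HRQoL. State whether the quartile is taken over the pooled cohort; quartiles taken within each country would make the share with a long interval equal by construction and remove country as a risk factor.
4. Label any threshold derived from HRQoL as exploratory. Otherwise correct it for the search with a maximally selected statistic, or validate it, for example by deriving it in one country and testing it in the other.

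Cost: wording only. No new data are needed, and no more patients for the baseline comparison: with 25% long and 10 points, power is 94% with 265 analysed and 88% with 212 (80% of 265). The small downside is that no data-derived threshold can be claimed as confirmatory.

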## Abstract

**Introduction:**

Sarcomas are rare tumours with considerable heterogeneity. Early and accurate diagnosis is important to optimise patient outcomes in terms of local disease control, overall survival (OS) and health-related quality of life (HRQoL). Time to diagnosis is variable in bone as well as soft tissue sarcoma. Possible factors for a long time from first symptom to diagnosis (the total interval) include patient, tumour and healthcare characteristics, but until now the most relevant risk factors and its association with outcomes remain unknown. Our study aims to (1) quantify total interval, the time interval from first symptom until (histological) diagnosis; (2) identify factors associated with interval length and (3) determine the association between total interval and HRQoL, stage and tumour size at diagnosis, progression-free survival (PFS) and OS.

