HRQoL is the patients’ perception of his overall health in relation to physical, psychological and social aspects in life.^14^ Three systematic reviews have been published on HRQoL of patients with sarcoma, however, none of these looked at the association of total interval length and HRQoL.^15–17^ In other cancers and chronic diseases, lengthening of total interval was associated with decreased HRQoL.^18 19^ HRQoL is an interesting outcome parameter for evaluating consequences of long total interval length and provides an insight into the patient’s experience of the consequences of diagnostic delay. In addition to using patient-reported outcomes as a measure for quality of care, HRQoL can be used to conduct cost-utility analysis to estimate the ratio between the cost of a prolonged total interval and the benefit of earlier diagnosis in terms of life-years (quality-adjusted life years (QALY)).

Until now, risk factors for a long total interval in adult sarcoma care as well as its effect on clinical and patient-reported outcomes remain unknown. These need to be studied in well-designed, large, prospective studies in order to prioritise interventions to optimise the total interval. Our study aims to quantify total interval, identify independent variables associated with a long interval (such as demographic and clinical factors) and determine the association between total interval and other dependent variables, such as HRQoL, stage and tumour size at diagnosis, progression-free survival (PFS) and OS (figure 1).

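### The risk-factor aim is analysed only by logistic regression on a long/short split of total interval, which discards information; the power lost depends on assumptions (about 24 points in a reference case)

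*Protocol article*

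**What the plan says.** The abstract gives the second aim as to "identify factors associated with interval length". The Introduction words it differently, as to "identify independent variables associated with a long interval".

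In Statistical analysis, the HRQoL question is approached by "plotting HRQoL against total interval length as a continuous variable", followed by linear regression. A cut-off is then taken from that analysis: "The time point providing a significant difference in HRQoL will be used as a cut-off point for further analysis". If no clear cut-off emerges, the Sample size calculation section states that "we will use the last quartile to define the population with a long total interval".

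For the risk factors, univariate logistic regressions are planned to "assess the relationship between total interval length (grouped by the cut-off point as defined by the previous analysis) and independent variables", namely patient, tumour and healthcare-system variables. Factors with p<0.1 go into one multiple logistic model by forced entry. No other model of the interval is named for this aim, and no power is stated for it.

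**The concern.** Total interval is the outcome of this aim. Once it is split, a patient just above the cut counts the same as the patient with the longest delay, and all ordering below the cut is lost. This happens wherever the cut falls and whether or not it was fixed in advance. How the cut is chosen is a separate matter.

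The Introduction says that the study should help to prioritise interventions on the interval. If power is low, a real but moderate factor may be screened out at p<0.1 or reported as not associated. An odds ratio for a long interval also does not show by how much a factor lengthens the interval.

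**Working it through.** **The plan's own figure.** The only sample size given is for HRQoL: a 10-point difference, SD 20, two-sided alpha 0.05, power 0.90, 25% long. The evaluable total is (1.960 + 1.282)² × (20/10)² × (1/0.25 + 1/0.75) = 10.51 × 4 × 5.333 ≈ 224. With 265 enrolled and 80% response, 212 are evaluable and power is about 88%, close to the stated 90%. This figure neither supports nor contradicts the present point, because nothing comparable exists for the risk-factor aim.

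**Inputs for the check.** From the protocol: 25% long (the fallback cut), two-sided alpha 0.05, screen at p<0.1, 530 patients (2 × 265). Assumed, because the documents do not give them: normal log interval, a factor present in half the patients, a pure shift in location, and an effect that gives 90% (or 80%) power in linear regression on log interval.

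**Information kept.** For a cut with upper fraction p, the efficiency relative to linear regression is φ(z)² / [p(1 − p)]. At p = 0.25: 0.3178² / 0.1875 = 0.539. So 530 × 0.539 ≈ 285 patients with an uncut outcome would carry the same information.

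**Power after the cut.** Power = Φ[(1.960 + z_power) × √0.539 − z_alpha], with √0.539 = 0.734.
- From 90%, at 0.05: Φ(3.242 × 0.734 − 1.960) = Φ(0.419) = 66.2%, a loss of 23.8 points.
- From 80%, at 0.05: Φ(2.802 × 0.734 − 1.960) = Φ(0.096) = 53.8%, a loss of 26.2 points.
- At the p<0.1 screen, for the same effect as in the 90% case: uncut Φ(3.242 − 1.645) = 94.5%; cut Φ(2.379 − 1.645) = 76.9%.

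Simulation agrees. At 530 patients the two models had 89.4% versus 64.9% power, and 79.7% versus 51.6%. At 265 patients they had 89.8% versus 68.5%.

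**How far the result moves.** Each line changes one assumption; the loss is against linear regression on log interval.

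| Assumption changed | Loss in points |
|---|---|
| Cut at the median | 16.6 (from 90%), 19.2 (from 80%) |
| Cut at the 90th percentile | about 42.5 |
| 20%-prevalent factor that lengthens the interval | about 16 to 22 |
| 20%-prevalent factor that shortens it | about 31 to 38 |
| Heavy-tailed log interval (t, 5 df), even split | about 11 to 17 |
| Log-Weibull errors, even split | about 0 (−4.5 to +1) |
| Right-skewed log interval (Gumbel), even split | about 34 to 43 |

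**Does the remedy depend on normality?** The rank-sum test is the univariate score test of a proportional-odds model on the uncut interval. It beat the last-quartile logistic model in every location-shift case run, by about 3 to 8 points under log-Weibull errors and by more elsewhere.

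**The case against.** **The target may be a long interval.** The Introduction speaks of risk factors for a prolonged or long interval, and a long/short outcome matches that wording. This stands as a reason to keep the logistic model. It does not make that model sufficient: the abstract says interval length, and Statistical analysis says that the multiple model tests independent association with total interval length.

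**The location-shift assumption favours linear regression.** This also stands. If a factor widens the spread of log interval by 1.5 without moving its mean, linear regression has about 6% power and the cut about 62% (530 patients, even split, last quartile). If a factor strongly delays only 10 to 15% of exposed patients, the cut loses about 11 to 16 points.

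**Dates carry error.** The Total interval section lets patient-reported dates stand unless more than 5% of those cross-checked differ from the record by over a month. With an assumed error SD of one month, the gap shrinks from about 26 to about 13 points at a 3-month median interval, and to about 19 at a 6-month median. The loss becomes smaller but does not vanish.

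**Stronger readings to avoid.** A reader might infer that the loss lies in a known, fairly narrow band. The documents do not support this: they give no distribution, prevalence or effect size, and the last quartile is only the fallback cut. A reader might also infer that the loss is suffered twice, in the screen and again in the multiple model. Both use the same data and nearly the same statistic, so the losses do not add up. Nor is it right that the cut has no clinical anchor: the plan refers it to published sizes of clinically relevant HRQoL difference, though not to any threshold for the interval itself.

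**Conclusion.** The point holds as a matter of analysis choice. The plan makes a long/short logistic model the only risk-factor analysis although the uncut interval is available and is used for another question. In the reference case (last-quartile cut, normal log interval, even-split factor, shift in location) the cut keeps about 54% of the information and costs about 24 points of power from 90%, or 26 from 80%. Elsewhere the cost runs from about 0 to over 40 points, and the documents cannot settle where this study lies. The logistic model is not invalid; it answers the narrower question of what predicts a long interval. A change is worth making because it is cheap and the possible gain is large.

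**What to change.** In Statistical analysis, name one model of the uncut interval as the main risk-factor analysis, univariate and multiple. Choose it in advance and not from the residuals. Either of these would serve:
- linear regression on log(total interval), reporting ratios of geometric means with 95% CI and a stated offset for zero intervals;
- a proportional-odds model on the uncut interval, which is less dependent on the shape of the distribution.

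Keep the long/short logistic model as a secondary analysis for the long-interval question, and use one wording of the aim in the abstract and Introduction.

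The cost is wording only; the data are the same and both methods are standard in the named software. There are two small downsides. The headline measure is no longer an odds ratio for a long interval. A factor that acts only on the upper tail would show mainly in the secondary model.
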